## 7. Postoperative follow-up and data collection

Postoperative follow-up consists of an in-person visit approximately 1 month after discharge and a telephone interview at 6 months. Data collected include current medications, pain intensity on a 1–10 numerical scale, use of analgesics, rehospitalizations, and adverse events categorized as cardiovascular, neurologic, bleeding-related, vascular-access-related, infectious, or other. Mortality after discharge will also be recorded. At 6 months, patients complete the EQ-5D-5L quality-of-life questionnaire. The complete list of variables, definitions, and measurement time frames is provided in S1 Table B (Follow-up questionnaires and variables at 1 and 6 months).

## 8. Sample size and statistical analysis

This is a pilot, exploratory randomized study comparing two surgical strategies (MICS vs. conventional CABG). The primary objective is to obtain descriptive estimates of event rates (rather than on hypothesis testing), between-group differences, and variability of outcomes to guide the design of a subsequent phase III trial.

The sample size of 100 patients (50 per group) was determined by operational feasibility and expected precision, rather than hypothesis testing. Assuming a conservative 8% 30-day MACCE rate (consistent with the average reported for conventional CABG in the 2025 ESC/EACTS Guidelines) the 95% confidence interval (Wilson) has a half-width of approximately ±5% in the overall cohort and ±7–8% per arm.

This approach aligns with published pilot trials in hybrid or minimally invasive CABG, which typically include 80–120 participants and use similar precision-based rationales.

Categorical variables will be presented as frequencies and percentages, and compared using the Chi-square or Fisher’s exact test, as appropriate. Continuous variables will be expressed as mean ± standard deviation or median (interquartile range) and compared using the Student’s t-test or Wilcoxon rank-sum test. Time-to-event outcomes (e.g., MACCE-free survival) will be analyzed using the Kaplan-Meier method.

No imputation for missing data will be performed, as this is a pilot trial focused on descriptive analyses rather than formal hypothesis testing. Missing data will be reported transparently, and analyses will be conducted using available cases.

All analyses will be performed according to the intention-to-treat principle. Participants randomized to the minimally invasive CABG group who require conversion to full sternotomy will remain in the MICS CABG arm for all primary and secondary outcome analyses. Conversion events will be reported descriptively, including their timing and reasons.

The decision to use or avoid cardiopulmonary bypass (on-pump or off-pump) will be left to the operating surgeon, according to intraoperative findings.

Any conversion from an off-pump to an on-pump procedure will be documented and analyzed descriptively but will not imply a change in group allocation. If protocol deviations or conversions occur, sensitivity analyses using a per-protocol approach may be conducted to assess the robustness of the findings. The per-protocol population will include patients who received the allocated intervention as planned and completed follow-up without major protocol deviations, such as conversion to sternotomy, incorrect surgical allocation, or loss to follow-up before 30 day.

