## 3. Methods and analysis

### 3.1. Study design

This is a single-center, prospective, randomized controlled pilot trial, conducted over 30 months. A total of 100 patients will be randomized to undergo either to minimally invasive CABG through left anterior thoracotomy in the 4^th^ or 5^th^ intercostal space or conventional median sternotomy CABG. The use of CPB will be at the discreet of the surgeon.

Patients will be randomized in a 1:1 ratio using variable block sizes (blocks of 4–8), generated and managed electronically within the REDCap platform. This method ensures balance between groups while minimizing the predictability of the next allocation. The randomization module was configured by an independent researcher not involved in patient enrollment or surgery. Participants will only be randomized after meeting all eligibility criteria and signing the informed consent form.

All patients will be operated on by the same surgical team, with the standardized technique, at a high-volume tertiary cardiac surgery center.

Informed consent approved by our institutional research and ethics in committee under the number CAAE: 54175921.8.0000.0068, will be applied to all participants prior to surgery.

Post-operative follow up will be of 6 months. The postoperative evaluations will be divided into an outpatient presential evaluation around 1 month from discharge, followed by telephone contact 6 months. Follow up maybe extended up to 2 years after the surgery by telephone contact, to collect descriptive mid-term data, depending on institutional feasibility and patient availability.

This protocol follows the SPIRIT 2013 guidelines for randomized clinical trial protocols. The SPIRIT schedule of enrolment, interventions, and assessments is shown in Fig 1.

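### Section 8 sets out to estimate between-group differences without testing, but the only between-group methods it names are significance tests; no difference with a confidence interval is named

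*Protocol article*

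**What the plan says.** All the relevant text is in Section 8 of the protocol article.

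- **Aim.** The primary objective is to "obtain descriptive estimates of event rates (rather than on hypothesis testing), between-group differences, and variability of outcomes", as input to a later phase III trial.
- **Sample size.** "The sample size of 100 patients (50 per group) was determined by operational feasibility and expected precision, rather than hypothesis testing". At an assumed 8% 30-day MACCE rate, the Wilson 95% interval "has a half-width of approximately ±5% in the overall cohort and ±7–8% per arm".
- **Missing data.** No imputation is planned, because "this is a pilot trial focused on descriptive analyses rather than formal hypothesis testing".
- **Between-group methods.** Categorical variables are "presented as frequencies and percentages, and compared using the Chi-square or" Fisher's exact test, as appropriate. Continuous variables are summarised by mean and SD or median and IQR, then compared by Student's t-test or the Wilcoxon rank-sum test. Time-to-event outcomes are analysed by Kaplan-Meier, with no between-group measure given.

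The only confidence interval in the section is the Wilson interval for a single proportion, in the sample-size paragraph. No alpha, sidedness or margin is stated.

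**The concern.** The aim and the named methods do not match. The section says three times (objective, sample-size basis, missing-data rule) that this is not a testing exercise, and it justifies the sample size by interval width. When it comes to comparing the arms, it names tests and nothing else. A p-value gives neither the size of a difference nor its precision, and these are what a pilot meant to inform phase III has to report.

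Safety at 30 days is a primary outcome (Section 6.1), and Section 9 describes a team still on its learning curve. With about 50 × 0.08 = 4 expected events per arm, a MACCE test will usually be non-significant even if the true difference is large. If the p-value is the only between-group result reported, the width of what remains possible is not shown.

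**Working it through.** **Inputs.** From Section 8: 50 per arm and 8% MACCE. Section 3.1 gives 1:1 allocation. Assumed, because the document gives none: two-sided 5%, control rate 8%, MICS rates of 12% to 24%.

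**1. The plan's own figure.** Wilson half-width = z√[p(1−p)/n + z²/(4n²)] / (1 + z²/n), with z = 1.96 and p = 0.08.
- n = 100: 1.96 × √(0.000736 + 0.000096) / 1.0384 = 0.054, interval 4.1% to 15.0%.
- n = 50: 1.96 × √(0.001472 + 0.000384) / 1.0768 = 0.078, interval 3.2% to 18.8%.

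Section 8's figures of about ±5% overall and ±7–8% per arm are reproduced. Both describe a single proportion, not a difference between arms.

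**2. The interval the aim calls for.** Newcombe's limits for d = p₁ − p₂, with Wilson limits (l, u) for each arm:

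lower = d − √[(p₁−l₁)² + (u₂−p₂)²]; upper = d + √[(u₁−p₁)² + (p₂−l₂)²].

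At 4/50 versus 4/50: √[(0.0800−0.0315)² + (0.1884−0.0800)²] = √(0.00235 + 0.01175) = 0.119, so 0 ± 11.9 points.

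Other outcomes by the same formula, MICS versus conventional:

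| Events | Difference (points) | Newcombe 95% CI (points) | Fisher p | Chi-square p |
|---|---|---|---|---|
| 4/50 v 4/50 | 0 | −11.9 to +11.9 | 1.00 | 1.00 |
| 8/50 v 4/50 | +8 | −5.3 to +21.4 | 0.36 | 0.22 |
| 12/50 v 4/50 | +16 | +1.5 to +30.3 | 0.054 | 0.029 |

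In the first row both tests return p = 1, yet a difference of nearly 12 points either way remains compatible with the data. In the third row the two permitted tests fall on opposite sides of 0.05, while the interval conveys the same information whichever test is chosen.

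**3. Power of the named tests.** Exact enumeration: sum Bin(a; 50, p_MICS) × Bin(b; 50, 0.08) over all pairs (a, b) with p ≤ 0.05. Chi-square is without continuity correction.

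| MICS rate (control 8%) | Fisher | Chi-square |
|---|---|---|
| 12% | 4.5% | 10.1% |
| 16% | 13.7% | 24.2% |
| 20% | 29.5% | 43.2% |
| 24% | 49.0% | 62.3% |

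For a doubling to 16%, the chance of a non-significant result is 100 − 24.2 = 75.8% (chi-square) to 100 − 13.7 = 86.3% (Fisher). If the test is chosen by the usual expected-count rule, power is 23.0%. By the normal approximation, 80% power for 8% versus 16% would need about 258 per arm.

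**The case against.** Four objections deserve an answer.

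- **The plan is not made up of tests alone.** Correct. Frequencies, percentages, means with SDs, medians with IQRs and Kaplan-Meier curves are all planned, and a reader could subtract the per-arm figures to get a point difference. A claim that the whole analysis is testing would be wrong. The point is confined to the between-group step, where no difference with an interval is named.
- **The interval method belongs in an SAP.** The choice between, say, Newcombe and Miettinen-Nurminen does, and an SAP that is not shown may provide intervals. But the article does name its between-group methods, and those do not fit its own stated objective. That mismatch would remain in Section 8.
- **No one says a non-significant result will be read as safety.** Also correct. A reader might infer it, but there is no margin or decision rule, and Section 9 says the size was not set for power and speaks only of preliminary safety signals. The misreading is a foreseeable risk, not a plan. Nothing in the text guards against it.
- **The figures depend on the test.** They do: the plan allows either test, and Fisher alone gives the lowest power. Both are therefore shown. Power for a doubling is low under either, but non-significance is likely rather than near certain.

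**Conclusion.** The concern holds within these limits. Section 8 makes between-group differences an object of descriptive estimation and disclaims testing, yet the only between-group methods it names are tests. The stated comparison does not give the precision of the difference the trial sets out to estimate. For MACCE that imprecision is large: ±11.9 points when both arms have 4/50 events. The tests have about 14% to 24% power against a doubling from 8%. The power figures rest on an assumed two-sided 5% level and assumed MICS rates; the intervals rest on illustrative event counts.

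A reader might also infer that phase III will be sized on the difference observed here. The documents do not say so. Section 8 lists between-group differences as one of several inputs to the later design, and the Abstract says only that the data will inform sample-size calculations.

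The feasibility outcome is not affected, since it is defined only for the minimally invasive strategy. The change should be made, but nothing in design or data collection depends on it.

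**What to change.** In Section 8, make the between-arm difference with a 95% confidence interval the main comparison:

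- binary outcomes, including 30-day MACCE: risk difference, by Newcombe or Miettinen-Nurminen;
- continuous outcomes: mean difference, or Hodges-Lehmann shift for skewed times and volumes;
- time-to-event outcomes: difference in Kaplan-Meier estimates at fixed times, such as 30 days and 6 months.

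Label any retained p-values exploratory, and add a sentence saying that a non-significant result is not evidence of equal safety.

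The cost is wording in the protocol and, if there is one, the SAP. The data and analysis effort are essentially unchanged. Section 3.2 reports that no results have been analysed, so the change can still be made before results are seen. The downside is that p-values lose prominence and the reported intervals will be wide, which is an honest picture of what 50 patients per arm can show.

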## 9. Patients and public involvement

Patients and the public were not involved in the design, conduct, reporting, or dissemination plans of this research.

Strengths and limitations of this studyMinimally invasive approach is growing trend in cardiac surgery.This is the first randomized trial comparing MICS-CABG with conventional surgery in Latin America.Conducted at a high-volume center performing approximately 700 CABG procedures per year.Pilot design with sample size based on feasibility benchmarks from similar surgical studies, such as hybrid revascularization trials.The sample size is feasibility-driven and was defined based on operational and logistical considerations rather than on statistical power to detect outcome differences. This design aims to assess the study’s feasibility, recruitment process, data collection workflow, and preliminary safety signals to inform future adequately powered trials, bridging the gap between highly experienced academic centers and real-world surgical settingsAlthough the center has published its experience with single vessel minimally invasive coronary artery bypass grafting (LIMA to LAD) more than 20 years ago, this is its first trial applying multiarterial minimally invasive cardiac surgery. As the surgical team progresses through a learning curve following short pre-trial training, this pilot phase is critical to assess feasibility and procedural standardization.The single-center design may limit generalizability to other institutions or healthcare systems.
